## Ethical approval

In November 2013, the study has been approved by the ethics committee of both universities involved in the project in Italy and The Netherlands.

## Discussion

This article presents the protocol of a study to assess feasibility, acceptability and potential effectiveness of an SDM framework in care planning for long‐term care residents with dementia. The aim of the study was to explore whether it is effective and feasible to take the dementia residents' personal perspective into account regarding assessing and meeting their own needs through an SDM process with the professional and family caregivers. Thus, SDM is here considered an opportunity for persons with dementia to express their opinion and wishes and care planning a comprehensive and constantly developing process that should be based on the residents' preferences, not only on the professionals' or family carers' perspective.

### Strengths and limitations

The key element of this study is that it will contribute to our knowledge about the efficacy and of SDM interviews in nursing homes with persons with moderate to severe dementia and will consider the barriers and facilitators to this practice in LTC settings. Besides, it will make an important contribution to test the feasibility for a full trial, as recommended by the United Kingdom Medical Research Council guidance on the development and evaluation of complex intervention (Craig *et al*. 2008). Moreover, the study will take place in nursing homes located in two different countries, Italy and the Netherlands: these data represent a source of interesting information on the application and feasibility of this study in countries characterized by different cultures and healthcare systems organization.

At the same time, cultural differences may affect the primary and secondary outcomes: these data are therefore collected and considered during data analysis. Furthermore, only a few nursing homes are recruited in this study: their organization and residents population may not be representative of these parameters in both countries. In addition, the supportive presence of the family caregivers during the SDM interview may influence the resident's behaviour and attitude. Therefore, this co‐variable will be taken into account.

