### Subjects and settings

Two nursing home wards in the Netherlands and two nursing home wards in Italy are involved. In each country, one ward will randomly be assigned to the intervention group and the other to the control group. The same number of residents, family caregivers and healthcare professionals will be assessed in both groups and the same tools will be used. In the Netherlands two Dementia Special Care (DSC) units in the same nursing home will be recruited, whereas in Italy two different nursing homes will be enlisted, being similar in numbers of residents admitted, staffing patterns and level of medical and psychosocial care provided, as described in their charters of services. To avoid contamination, in the Netherlands the professionals working in the experimental DSC unit will not be the same as the ones working in the control DSC unit.

In each experimental and control nursing home ward, 20 dementia residents will be included, based on the following inclusion criteria: (1) having a diagnosis of dementia based on DSM IV (American Psychiatric Association 2000); (2) being able to give informed consent or, if legally incapable, having a family caregiver who can give informed consent for them; and (3) being supported by one primary family caregiver who agrees to participate and to be involved in the study too.

Inclusion criteria for the principal professional caregivers are: (1) being a member of the multidisciplinary team who is used to being directly involved in the care planning process; and (2) being a key staff member in the provision of residents' care and consequently to know the identified residents well. In both countries, at least eight healthcare professionals will be recruited to attend the training provided for the project and will later conduct the SDM interviews with 20 residents and their family caregivers.

Thus, the entire experimental group is composed by a total of 40 dementia residents, 40 family carers and about 16 healthcare professionals. These participants will be compared with the two other control nursing home wards that will be asked to involve the same number of subjects. After the selection is completed, a researcher will check the accuracy of the choices based on the requested inclusion criteria.

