***Patient***			
Needs assessment	Camberwell Assessment of Needs in the Elderly (CANE)	R/FC/C	R/FC/C
Level of dependency	Katz Activities of Daily Living index (ADL)	P/C	P/C
*Primary outcome measure*			
Documentation of residents' preferences and of the actions taken to satisfy them	Proportion of residents whose preferences and needs' satisfaction is documented	DR	DR
*Secondary outcome measure*			
Quality of life	Dementia quality of life Instrument (DQoL*)*	R	R

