#### c) Phase 2 – SDM conversation

The SDM conversation will take place between a triad, composed of the resident with dementia, the family caregiver and the LTC professional as facilitator. The professional will be taught to tell the resident and the family caregiver that the aim of the consultation is to tailor the ‘life‐and‐care plan’ to the resident's actual needs and preferences. Using the unmet needs as collected with the CANE, as starting point, the main steps of the SDM process that will be applied during the conversation are: (a) identification of problems and needs; (b) prioritization of the most important problems or needs to set the intervention's goals; (c) discussion of options and preferences and (d) identification of actions. The role of the family caregiver is to support and facilitate the resident's expression: if communication is limited, the family caregiver is stimulated to intervene, to add information and to stimulate the person with dementia. Together, the participants in the consultation will make plans to comply with the prioritized needs and will develop actions to meet them.

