## Data analysis

Quantitative data will be analyzed using the Statistical Package for Social Science (SPSS). The proportion of residents whose SDM documentation on needs satisfaction has been fulfilled, will be analyzed using the Fischer's exact test. Secondary outcomes, at the level of residents, professional and informal caregivers, will be calculated using parametric and non‐parametric tests, making comparison between and within groups. Descriptive statistics will be used to compare the experimental and control nursing home wards for socio‐demographic characteristics and baseline variables. In each country, the focus group discussions' content will be translated into English. Two independent researchers will code the data by using a constant comparative method (Johnson *et al*. 2012). Each researcher will develop and label categories with appropriate codes outlining the core concepts of the focus group interviews. Then, the codes will be combined in clusters to define the concepts and identify similarities and differences between the interviews (Boeije 2002). Codings will be discussed until consensus will be reached.

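### The one primary test named, Fisher's exact test, appears to use neither country nor the baseline documentation review, although the protocol says cultural differences will be considered in the analysis

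*Protocol article*

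**What the plan says.** - **Allocation.** Subjects and settings: "In each country, one ward will randomly be assigned to the intervention group and the other to the control group". Each ward includes 20 residents. The section then describes one experimental group of 40 and compares it with the two control wards.
- **Primary analysis.** Data analysis: the proportion with fulfilled documentation "will be analyzed using the Fischer's exact test". No stratum, covariate or baseline term is named.
- **Other analyses.** For secondary outcomes the same section plans parametric and non-parametric tests, "making comparison between and within groups". For baseline variables, "Descriptive statistics will be used to compare the experimental and control nursing home wards".
- **Baseline measurement of the primary outcome.** Table 1 lists "Documentation of residents' preferences and of the actions taken to satisfy them" by documentation review at baseline and at six months. The primary outcome section describes the determination only at six months.
- **Country.** Strengths and limitations: "cultural differences may affect the primary and secondary outcomes: these data are therefore collected and considered during data analysis".
- **Family presence.** The same section notes that "the supportive presence of the family caregivers during the SDM interview may influence the resident's behaviour and attitude" and says that this co-variable will be taken into account. Under Phase 2, "The SDM conversation will take place between a triad", and the family caregiver is a member of that triad. A participating family caregiver is also an inclusion criterion.

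**The concern.** Country is a design stratum, and the authors themselves expect that it may matter. A single two-by-two table of arm by outcome has no place for a stratum, a covariate or a starting value. The stated intention and the named method therefore do not meet.

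The baseline gap is similar. With four wards, and two different nursing homes in Italy, equal documentation at the start cannot be assumed. The data that would show and correct an imbalance are collected, yet no inferential use of them is named for the primary outcome.

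Family presence raises a smaller point. It is called a co-variable, but as defined it cannot vary in a way that a between-arm analysis could use.

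At stake are the precision of the estimate, and whether a difference that existed before the intervention is credited to shared decision-making.

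**Working it through.** The article states no alpha, power, effect size or expected rate, so there is no power figure of its own to reproduce. The head count agrees: 2 × 20 = 40 residents per arm and 4 × 20 = 80 in all.

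**1. The estimate under pooling.** Let d1 and d2 be the risk differences in the two countries.
- Pooled difference: (20·d1 + 20·d2)/40 = (d1 + d2)/2.
- Mantel-Haenszel weight per country: 20 × 20/(20 + 20) = 10, so the combined difference is (10·d1 + 10·d2)/20 = (d1 + d2)/2.

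The two are identical at the planned ward sizes. Country is balanced across arms and does not confound.

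**2. Power and test size.** Assumptions, none from the article: two-sided alpha 0.05, common odds ratio 4, 20 per ward, independent residents. The pooled Fisher test (40 v 40) is compared with an exact conditional test stratified by country, by full enumeration.

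| Control rates in the two countries | Power, pooled | Power, stratified | Actual size, pooled |
|---|---|---|---|
| 40% / 40% | 80.6% | 80.6% | 3.0% |
| 20% / 60% | 66.4% | 71.5% | 1.7% |
| 10% / 70% | 35.5% | 55.9% | 0.6% |

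The stratified test keeps a size of about 3% in all three rows. At a milder 20%/40% the powers are 77.2% and 77.8%.

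The last row shows the mechanism. An odds ratio of 4 turns 10% and 70% into 30.8% and 90.3%, so the arm averages are 60.5% and 40% and the difference is about 20.5 points.
- Country-stratified variance: (0.308×0.692 + 0.903×0.097 + 0.1×0.9 + 0.7×0.3)/(4×20) ≈ 0.600/80 = 0.0075, standard error 8.7 points.
- Pooled variance: (0.605×0.395 + 0.4×0.6)/40 ≈ 0.479/40 = 0.0120, standard error 10.9 points.

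The estimate is the same, but pooling attaches a larger error to it.

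**3. Opposite effects.** If one country gave 14/20 v 6/20 and the other 6/20 v 14/20, each has p = 0.026, while the pooled table is 20/40 v 20/40 with p = 1.0. This is an extreme case, but it shows what a single table can hide.

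**4. Baseline.** Suppose shared decision-making has no effect and starting differences persist. From step 1, the pooled six-month difference is (x + x)/2 = x if both pairs differ by x in the same direction, and (x + 0)/2 = x/2 if only one pair does. For example, x = 25 points in both pairs could give 28/40 v 18/40, for which Fisher's p = 0.041.

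**5. Family presence.** Presence is constant across shared decision-making conversations, because the caregiver belongs to every triad. Training is given only in the intervention wards and no such conversation is described for controls, so presence is undefined there. Coding it as absent in controls makes it equal to arm: a design matrix with intercept, arm, country and presence for 80 residents has 4 columns but rank 3. The coefficient cannot be estimated.

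**The case against.** **Pooling is an inference.** The article does not say that the test is run across countries, and separate tests by country are not excluded. A fuller plan may add stratification. This stands as a caveat, but the combined group of 40 compared with the two control wards makes pooling the natural reading.

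**Country may be considered in other ways.** Setting descriptors are collected, and the focus groups discuss national factors. That meets the intention in part, but it does not bring country into the quantitative comparison.

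**Pooling might be thought to bias the result.** A reader might infer that pooling pulls the effect towards the null. It does not bias the planned comparison. The outcome is a proportion, no odds ratio is planned, and the risk difference is unchanged. A pooled odds ratio would be smaller than the within-country one, but in a balanced design that is non-collapsibility, not confounding. Under independence the pooled test is conservative, so pooling creates no false positives. The power loss is near zero unless the rates differ widely, and the article says only that culture may affect outcomes.

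**Baseline is not wholly ignored.** Wards are to be compared descriptively, so an imbalance could be seen. The six-month outcome also draws on plans updated after the conversation, so baseline status may be low everywhere or not fully comparable, and adjustment may then add little. Both points stand, but neither gives the primary comparison a way to use the baseline review.

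**Family presence.** A reader might infer a promise to adjust the between-arm test for presence, with the treatment effect removed as a result. The article promises only to take it into account, which description within the intervention arm would satisfy. An aliased term is not estimable; it does not adjust the effect away.

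**Conclusion.** The concern holds as a mismatch between the stated intention and design on one side and the single named primary test on the other. It is a loss of information, not an invalid estimate.

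- **Country:** the cost runs from nothing at equal control rates to about 5 points of power at 20%/60% and about 20 points at 10%/70%. All of these rest on an assumed odds ratio of 4, independent residents and rates that the article does not give.
- **Baseline:** a starting ward difference enters the result as x or x/2, depending on whether both country pairs or only one is affected, if it persists to six months.
- **Family presence:** it cannot be estimated as a between-arm covariate, whatever analysis is chosen.

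This is a feasibility study, so clear estimates by country matter more than the test. Nor does stratifying cure the larger limit: with one ward per arm per country, ward effects cannot be separated from the intervention. Under an assumed intraclass correlation of 0.05 and a 30% rate, the pooled Fisher test has a type I error of about 12%. The conservatism shown above therefore depends on independence.

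**What to change.** 1. Report the risk difference within each country, and combine the two with Mantel-Haenszel weights and a country-stratified variance. If a test is kept, use an exact test stratified by country.
2. Use each resident's baseline documentation status, either by adjustment or as change from baseline. Define that status so that it can be read in the same way in both arms before any conversation has taken place.
3. Replace the wording on family presence as a co-variable with a description of family involvement within the intervention arm only.
4. State that none of this separates ward effects from the intervention.

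The cost is a few lines in Data analysis and in Strengths and limitations. Country is known for every resident and the baseline documentation review is already scheduled, so no new data are needed.
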